### **Interim analyses**

No interim analyses are planned in this study.

### **Statistical analysis**

Characteristics of patients and baseline comparisons

Baseline characteristics will be presented by treatment group. Frequency and percentages will be used to describe categorical variables, and means and standard

deviations (SDs) or interquartile range used to describe normally distributed continuous data. We considered the independent sample test or the non-parametric Mann-Whitney test for continuous outcomes, and the  $\chi^2$  test or Fisher's exact test for categorical outcomes.

The following baseline characteristics will be presented:

- Age
- Parity
- body mass index
- smoking history
- time
- since menopause
- use of hormone replacement therapy
- medical and obstetric history,
- previous pelvic floor
- gynecological surgery

### **Description of analyses**

#### Primary outcome

The primary outcome measure is a composite surgical success variable measured at 1 year after surgery, defined as follows:

1. Absence of vaginal bulge symptoms as indicated by a rating of 0 on question 3 of the Pelvic Floor Distress Inventory-20 (PFDI-20): "Do you usually have a bulge or something falling out that you can see or feel in your vaginal area?"
2. No additional re-treatment (surgical or not) for POP
3. No POP-Q point at or beyond the hymen (i.e., Aa, Ba, C, Ap, Bp all < 0 cm)

All estimated difference with their 95% confidence intervals in primary outcome will be reported, the Agresti-Coull method will be used to calculate 95% CIs for differences in proportions.

We will apply multiple imputation techniques (five imputed datasets) for all women with missing data on primary outcome. Robustness of primary outcome will be

evaluated in sensitivity analyses performed in the ITT population without imputation. We will also conduct a secondary analysis of primary outcome based on per-protocol population, which excludes all patients who had a protocol deviation.

The secondary outcomes

- Anatomic outcome (POP-Q score) of each vaginal segment
- Symptomatic improvement-relief of symptoms of pelvic floor disorders, including urinary, bowel and sexual function using validated instruments
- Intraoperative parameters
- Complications
- Costs, defined as the direct total charges for the surgical admission including operation, medication and use of materials (e.g., surgical mesh)

We will consider the independent sample test or the non-parametric Mann-Whitney test for continuous outcomes, and the  $\chi^2$  test or Fisher's exact test for categorical outcomes. We will use paired sample t test to compare mean continuous data within groups. For anatomic outcomes (POP-Q score) and symptomatic improvement outcomes, we will compare the changes from baseline to 1-year follow up.

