### **Study design**

The trial is a randomized controlled multi-center non-inferiority trial. The study protocol and informed consent was approved by the institutional review board of Peking Union Medical College Hospital. The trial was registered with [www.clinicaltrial.gov](http://www.clinicaltrial.gov) (NCT03283124). Patients will be recruited from 11 hospitals at Tier III level in China. The gynecology department in each participating hospital performed at least 50 POP surgeries each year. In order to facilitate research development beyond this single trial, a new electronic data capture (EDC) system was co-developed with a CRO [LinkDoc Beijing company] and they will be responsible for data management. The CRO will have no role in the analysis of the data or the eventual production of any research manuscripts.

All women eligible at each center will be invited to participate. It is not possible to blind surgeons to the allocated surgical procedure. Women were not able to be blinded because payment for the cost of the implant is paid directly to the hospital by the patient, and they necessarily informed about the difference in cost between the two mesh products as part of the consent process. An independent staff or a research nurse who was not involved in treatment will carry out the questionnaires collection and follow-up POP-Q measurement. A figure showing the planned visit and examination schedule is presented in Fig.1 and Fig.2.

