## **Randomization**

After informed consent is signed, the patients will be registered on the web-based EDC system by a research staff to allocate each a unique study number prior to randomization. Research staff will access the system and, using the study number and initials, request randomization. Patients are randomized in a 1:1 ratio to either "self-cut mesh" group or "mesh-kit" group, according to a computer-generated randomization sequence with a block size of six. Randomization will be stratified according to centers. The patient and surgeon will be informed about the allocated operative procedure after the randomization.

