### **Data analysis**

Data was analyzed on an intention-to-treat basis. Frequency and percentages were used to describe categorical variables, Fisher's exact test used to compare treatment groups, and logistic regression used to estimate odds ratios (ORs), and associated 95% confidence intervals (95% CIs). Means and standard deviations (SDs) were used to describe approximately normally distributed continuous data. Analysis of covariance (ANCOVA) was used to compare treatment groups at 1 years after

procedure adjusting for baseline values and to estimate mean differences between treatment groups and associated (95% CI). Medians and range (minimum, maximum values) were used to describe non-normally distributed continuous data, Wilcoxon rank sum test used to compare treatment groups and Student t test to estimate mean differences and associated (95% CI). Paired t tests were used for differences between pre- and post-measurements. For the primary outcome, we will also perform subgroup analysis based on body mass index (BMI) ( $< 24$ ,  $\geq 24$ ), history of POP procedure(primary, recurrent), or prolapse stage (stage 3, stage 4). Analyses will be performed for each subgroup in a similar way to the primary analysis. AEs will be listed and analyzed using a  $\chi$ -squared test or Fisher's exact test. Severe AEs will be listed and described in detail.

All data will be analyzed with SPSS 21.0 (IBM, Chicago, IL, USA) software packages. Statistical significance is defined as a two-sided P value of  $< 0.05$ .

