## **Final statistical analysis plan**

### **Analysis principles**

- Analyses will be by intention-to-treat, which included all patients assigned to their randomly allocated surgery, irrespective of actual interventions undertaken.
- If there are any important imbalance in the baseline characteristics between groups, we will use logistic regression adjusting for baseline covariates for binary outcomes, and use linear regression analysis adjusting for baseline variables.
- Some important baseline characteristics will be the subject of possible subgroup analysis (see below). Whether or not the characteristics are associated with a different treatment outcome will be tested by an interaction term between the characteristic and the treatment.

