### **Justification of the sample size**

The aim of the trial is to test the hypothesis that the procedure with self-cut mesh is non-inferior to the procedure with a mesh kit in terms of the composite success rate and safety. According to Fünfgeld et al.'s report, the anatomic success rate (POP-Q stage  $\geq$  II, different from this proposed study) after 12 months across all compartments was 86%. Based on a success rate of 90% in this study and 10% as the non-inferiority margin ( $\beta = 0.2$  and one-sided  $\alpha = 0.025$ ), 284 patients (142 in each group) would be required. Taking into account 10% who do not continue to the 1-year follow-up visit, a total of 316 patients will be recruited. The procedure with self-cut mesh will be considered non-inferior if the lower limit of the 95% confidence interval in success rates lies above the non-inferiority margin of -10%. The enrollment will be more than 10 patients in each center.

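### The primary interval leaves out the centre strata, and the only adjustment planned hangs on an undefined imbalance and yields an odds ratio, a scale on which the plan has no margin

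*Combined protocol and SAP*

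**What the plan says.** **Design.** Current protocol, Study design: "Patients will be recruited from 11 hospitals at Tier III level in China". Current protocol, Randomization: "Randomization will be stratified according to centers", using a "computer-generated randomization sequence with a block size of six". The final SAP's sample-size section adds: "The enrollment will be more than 10 patients in each center".

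**Primary analysis.** Final SAP, Primary outcome: "the Agresti-Coull method will be used to calculate 95% CIs for differences in proportions". No strata are named. The claim requires that the "lower limit of the 95% confidence interval in success rates lies above the non-inferiority margin of -10" per cent. Missing primary outcomes are multiply imputed in five datasets. Centre has no role in the planned analyses. It is not in the primary analysis, the listed baseline characteristics or the subgroups.

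**Adjustment.** Final SAP, Analysis principles: "If there are any important imbalance in the baseline characteristics between groups, we will use logistic regression adjusting for baseline covariates for binary outcomes". The protocol's Data analysis section gives the scale of that model: "logistic regression used to estimate odds ratios (ORs), and associated 95% confidence intervals (95% CIs".

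**The concern.** In a non-inferiority trial one lower bound decides the claim. The plan should therefore fix in advance which analysis gives that bound and on what scale.

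- **Strata.** Balancing by centre and then ignoring centre gives up some of the precision that stratification can provide.
- **Trigger.** Whether an adjusted analysis exists depends on how the baseline tables look. The SAP does not say what counts as important, which covariates enter, or what standing the result has. Patients and surgeons know the allocation, so a rule fixed in advance matters more here than in a blinded trial.
- **Scale.** If the trigger fires, the described output is an odds ratio. The documents contain no odds-ratio margin and no conversion to a risk difference, so the result cannot be set against -10 points.

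**Working it through.** **1. The plan's own figures.** Inputs from the sample-size sections: 90% success in both arms, margin 0.10, one-sided alpha 0.025, power 80%.

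n per arm = (1.960 + 0.842)² × 2 × 0.9 × 0.1 / 0.10² = 7.85 × 18 = 141.3, so 142 per arm and 284 in all. Then 284 / 0.9 = 315.6, so 316. Both SAP figures reproduce.

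**2. Cost of leaving out centre.** The documents give no between-centre variation, so it is assumed here: all centres at 90%, or centres spread evenly over 85-95% or 80-100% (SD 0, 3.2 and 6.3 points). The simulation used 284 patients, 11 near-equal centres, blocks of six and 40,000 runs. The SAP does not write out its formula. It is read here as a Wald interval after adding one success and one failure per arm. The comparator is the Mantel-Haenszel risk difference,

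RD = Σ wₖdₖ / Σ wₖ, with wₖ = n₁ₖn₀ₖ / Nₖ,

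with the Sato variance. Error is evaluated with the true difference at -10 points in every centre.

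| Centre rates | Power, unstratified | Power, stratified | Error, unstratified | Error, stratified |
|---|---|---|---|---|
| all 90% | 79.6% | 80.1% | 2.7% | 2.8% |
| 85-95% | 79.8% | 80.6% | 2.6% | 2.7% |
| 80-100% | 80.2% | 82.0% | 2.5% | 2.7% |

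Mean half-width at no difference is 7.1 points unstratified against 6.9, 6.9 and 6.8 stratified. A separate simulation at 142 per arm gave power of 80.0 v 80.6%, 79.8 v 80.7% and 79.5 v 81.3%, with error of 2.5-2.8% for both methods.

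A gain near 3 points needs a centre SD of about 10 points. By the normal approximation:

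- Within-centre variance: 0.09 - 0.01 = 0.08.
- Standard error: √(2 × 0.08 / 142) = 0.0336, and 0.1 / 0.0336 = 2.98.
- Stratified power: Φ(2.98 - 1.96) = 84.6%.
- Unstratified power: the standard-error ratio is √(0.08 / 0.09) = 0.943, so Φ(2.98 - 1.96 / 0.943) = 81.6%.

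**3. The margin as an odds ratio.** Odds ratio for a 10-point loss:

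- from 90%: (0.80 / 0.20) / (0.90 / 0.10) = 0.444
- from 86%: (0.76 / 0.24) / (0.86 / 0.14) = 0.516

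The SAP cites 86% from an earlier study and assumes 90%, so its own figures give two answers. Read the other way, an odds ratio of 0.444 means -16.0 points at 80% control success, -12.8 at 86%, -10.0 at 90% and -5.6 at 95%.

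**4. How often the trigger might fire.** The SAP provides for significance tests of baseline characteristics but does not say that they define an important imbalance. If they did, at 0.05 and with independent tests (both assumptions), at least one would be significant by chance with probability 1 - 0.95⁸ = 34% for 8 tests and 1 - 0.95¹⁰ = 40% for 10. Prolapse stage, one of the SAP's subgroup factors, is not among the listed baseline characteristics, so a trigger based on that list would not check it.

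**5. Room for an adjusted model.** Expected failures: 284 × 0.10 = 28.4. Intercept, treatment, 10 centre indicators and 3 covariates make 15 parameters, about 1.9 failures each. A centre of 11 patients has no failures with probability 0.9¹¹ = 31%, and a centre indicator with no failures causes separation.

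**The case against.** The best defence is that the decision is already fixed. The margin is on the difference in success rates, the interval method is named, and nothing says that an adjusted model displaces it. With no odds-ratio margin anywhere, the natural reading is that the logistic regression is supportive. In step 2 the unstratified interval keeps error near nominal and power near 80%. Most of this stands. It leaves the trigger undefined, the standing of its result unstated and its scale unconnected to the margin.

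Five stronger readings are tempting, and the documents do not support them:

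- **The analyst may pick the model that decides the claim.** The SAP is silent on replacement. It does not grant that choice.
- **The trigger is a baseline test at 0.05.** This is inference, so the 34-40% is only illustrative.
- **The unstratified interval is clearly conservative.** A normal approximation with variance 0.09 gives error of 0.023-0.019 at centre SDs of 5-10 points. But error is judged at the margin, with arms at 90% and 80% and mean variance (0.09 + 0.16) / 2 = 0.125, which gives 0.024-0.0205. That formula also ignores the added pseudo-counts. Simulation of the interval, up to an SD of 6.3 points, gave 2.5-2.8%.
- **Five Agresti-Coull intervals cannot become one bound.** Each dataset gives an adjusted estimate and variance, which Rubin's rules can combine. The SAP simply does not say so.
- **A logistic model cannot address the margin.** Standardised over the trial population, it gives a risk difference. The gap is that the plan does not specify this.

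One caution applies to both methods. The error rates above assume the same difference in every centre. In simulations with centres drawn at random, a constant odds ratio and the -10 points defined over the population of centres, error rose for both: 2.9% unstratified v 3.2% stratified at a log-odds SD of 0.5, and 3.8% v 4.5% at 1.0 (near-equal centres). Neither interval allows for the sampling of centres, so stratifying is no remedy for that.

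**Conclusion.** The point holds, with unequal weight on its two parts. The conditional adjustment is the more serious: it has no threshold, no covariate list and no stated standing, and its described output is an odds ratio that cannot be compared with the -10 point margin. This follows from the text and needs no assumption.

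The omission of centre is a modest loss of efficiency. Stratifying adds about 0.5 to 2 points of power for assumed centre rates from all 90% to an even 80-100% spread, and about 3 only at an extreme SD near 10 points. Error is about 2.5-2.8% either way if the difference is the same in every centre. These figures rest on the assumed spread, near-equal centres and the add-one reading of the interval. The unstratified interval does not invalidate the trial or leave it materially short of power.

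**What to change.** 1. **Primary analysis.** Use a Mantel-Haenszel risk difference stratified by centre, computed in each imputed dataset and pooled by Rubin's rules. Declare non-inferiority if the lower 95% bound is above -10%. The estimate stays defined when a centre has no failures.
2. **Sensitivity analysis.** Keep the unstratified Agresti-Coull interval, write out its formula, and pool its estimate and variance the same way.
3. **Adjustment.** Delete the imbalance trigger. Prespecify one supporting adjusted analysis, stated not to replace the primary: a logistic model with prolapse stage, primary or recurrent prolapse, and BMI, reported as a standardised risk difference with its 95% interval. Leave the 10 centre indicators out of it because of the separation risk.

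The cost is SAP wording and a few lines of code, settled before outcomes are compared by arm. No new data or patients are needed. The downsides are slightly more analysis work and reliance on the Mantel-Haenszel variance in small centres.

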### **Statistical analysis**

#### **sample size and power considerations**

The aim of the trial is to test the hypothesis that procedure with self-cut mesh is non-inferior to the procedure with a mesh kit in terms of the composite success rate and safety. According to Fungfeld's report, the anatomic success rate (POP-Q stage  $\geq$  II, different from this proposed study) after 12 months across all compartments was 86% [8]. Based on a success rate of 90% in this study and 10% as the non-inferiority margin (beta 0.2 and one-sided alpha 0.025), 284 patients (142 in each group) would be required. Taking into account 10% who do not continue to the 1-year follow-up visit, a total of 312 patients will be recruited. the procedure with self-cut mesh will be considered non-inferior if the lower limit of the 95% confidence interval in success rates lies above the non-inferiority margin of -10%.

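### Five imputations with no recorded seed leave the primary non-inferiority limit slightly dependent on chance; at least 50 with a fixed seed would be a free, minor improvement

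*Combined protocol and SAP*

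**What the plan says.** The final SAP (Description of analyses, Primary outcome) states: "We will apply multiple imputation techniques (five imputed datasets) for all women with missing data on primary outcome". The intention-to-treat analysis without imputation is listed there as a sensitivity analysis, so the imputed result is the primary one. For the interval, "the Agresti-Coull method will be used to calculate 95% CIs for differences in proportions". The decision rule, under Justification of the sample size, is that the self-cut procedure is "non-inferior if the lower limit of the 95% confidence interval in success rates lies above the non-inferiority margin of -10" per cent.

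The final SAP gives no random seed, imputation model, rule for pooling the interval across imputed datasets, or check of Monte Carlo error.

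On the amount of missing data, it says: "Taking into account 10% who do not continue to the 1-year follow-up visit, a total of 316 patients will be recruited". The revised protocol (Data collection, COVID-19 adjustments) lets women who cannot attend at 1 year be followed by telephone, with examination later when possible. A telephone contact can supply the questionnaire items but not POP-Q, which the composite needs.

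**The concern.** Multiple imputation adds random noise that depends on the seed and shrinks as the number of imputations, m, grows. Five is often defended because the point estimate loses little efficiency. Here, though, the claim rests on a confidence limit. That limit carries the noise in the pooled estimate and also the noise in a between-imputation variance estimated from only five values. With no seed fixed, two analysts who follow the SAP exactly on the same data could report different limits. If those limits fell on either side of -10 points, the two would reach opposite conclusions.

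**Working it through.** **Inputs.** "Based on a success rate of 90% in this study and 10% as the non-inferiority margin" (final SAP); "beta 0.2 and one-sided alpha 0.025" (protocol, sample size and power considerations); "284 patients (142 in each group) would be required"; "Patients are randomized in a 1:1 ratio" (protocol, Randomization); 316 recruited, so 158 per arm; m = 5.

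**The plan's own figure.** n per arm = (1.960 + 0.842)² × 2(0.9)(0.1) / 0.10² = 141.3, rounded up to 142, so 284 in total. 284 / 0.9 = 315.6, rounded up to 316. Both SAP figures reproduce. The protocol's 312 matches 284 × 1.1 = 312.4; the difference does not affect this point.

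**Model for the seed effect.** Let f be the fraction of missing information. The total variance with unlimited imputations is T = 0.18 / (158(1 − f)), and the between-imputation variance is B = fT. At f = 0.10:
- T = 0.18 / 142.2 = 0.001266, a standard error of 3.56 points.
- B = 0.0001266.
- Power with unlimited imputations = Φ(0.10/0.0356 − 1.96) = 80.3%.
- Seed noise in the pooled estimate alone = √(B/m) = 0.50 points at m = 5 and 0.16 at m = 50.

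Each simulated run takes the data estimate, adds N(0, B/m), estimates B on m − 1 degrees of freedom and forms Rubin's t interval. Two independent runs per trial are compared with -10 points, over 200,000 trials.

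| Missing information | Opposite verdicts, m = 5 | m = 50 | Power, m = 5 | m = 50 |
|---|---|---|---|---|
| 5% (assumed) | about 3% | about 1% | about 82% | about 82% |
| **10% (planned loss)** | **5.4%** | **1.6%** | **79.1%** | **80.0%** |
| 20% (assumed) | 10.3% | 2.7% | 72.5% | 75.2% |
| 30% (assumed) | 15.6% | 3.9% | 64.5% | 69.3% |

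At 10%, the seed-to-seed SD of the lower limit is 0.60 points with m = 5 and 0.17 with m = 50. Repeat runs agree to within about 0.1 point for opposite verdicts and about 0.4 points for power.

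**Second method.** Binary outcomes were imputed by arm from a Beta posterior, with one success and one failure added per arm (an Agresti-type adjustment), Rubin pooling and 40,000 trials per scenario. At 10% missing, opposite verdicts were 5.5% (m = 5), 2.6% (m = 20), 1.6% (m = 50) and 1.1% (m = 100). Power was 78.9%, 79.9%, 80.0% and 80.0%. With true rates of 80% v 90%, where non-inferiority is false, it was declared in 2.7% of trials with m = 5 and 2.6% with m = 100.

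**Where it bites.** Take 128/142 observed successes in the mesh-kit arm and 16 women missing per arm. The share of seeds declaring non-inferiority is:

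| Self-cut successes of 142 | m = 5 | m = 20 | m = 50 | m = 100 |
|---|---|---|---|---|
| 123 | 4% | 0% | 0% | 0% |
| 124 | 33% | 23% | 13% | 5% |
| 125 | 78% | 96% | 99.8% | 100% |
| 126 | 97% | 100% | 100% | 100% |
| 128 | 99.9% | 100% | 100% | 100% |

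Only results within a few patients of the boundary are affected.

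**The case against.** The strongest reply is that the effect is small at the planned loss. Power falls by about 1 point, and type I error does not move. The 5.4% compares two noisy runs; the chance that a single five-imputation run differs from the unlimited-imputation verdict is about 3.8%. The planned analysis without imputation needs no seed and could expose a borderline case. Recording a seed would by itself make the result repeatable, and 20 imputations recover nearly all the power. All of this stands, and it is why the point is minor. But the sensitivity analysis does not replace the primary verdict, and a fixed seed with m = 5 makes an arbitrary limit repeatable without making it more precise.

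A reader might infer more than the documents support:
- *That five imputations make a false claim of non-inferiority more likely.* The type I error figures show no such effect.
- *That a t-quantile on few degrees of freedom widens the interval.* At 10% missing information and m = 5 there are about 289 degrees of freedom (t = 1.968 against 1.960). Even at an assumed 30% there are about 35 (t = 2.031).
- *That the pandemic pushed missing data to 20–30%.* The documents give no share above 10%. The revised protocol still collects questionnaires by telephone and encourages a later examination, so some POP-Q data may be late rather than lost.
- *That the missing share equals missing information.* That holds only without useful predictors. A woman who reports a bulge or re-treatment by telephone is already a failure under the composite, and the Fig. 2 schedule includes POP-Q at 3 months. An imputation model that uses such data could lower the fraction.

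**Conclusion.** The point holds as a modest weakness in the precision and reproducibility of the deciding analysis. At the planned 10% loss, about 1 trial in 18 (1/0.054 = 18.5) would give opposite verdicts under two seeds, against about 1 in 60 (1/0.016 = 62.5) with 50 imputations, and power is about 1 point lower. These figures assume 90% success in both arms, 158 per arm, values missing at random, missing information equal to the missing share, and Rubin pooling, which the SAP does not itself specify. Under the assumed range, disagreement with m = 5 runs from about 3% (5% missing information) to about 16% (30%), against about 1% to 4% with m = 50. The power loss runs from about 0.4 to 5 points. It is not a validity error, and a result well away from -10 points would not be affected.

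**What to change.** In the final SAP, Primary outcome, replace five imputed datasets with *at least 50 imputed datasets, generated with a prespecified and recorded seed*. Add that the Agresti-type adjustment is applied within each imputed dataset and that the adjusted risk difference and its variance are then pooled by Rubin's rules, with the lower 95% limit taken from the pooled result. The choice of 50 is a judgement: 20 recovers most of the power, while 50 to 100 further reduces dependence on the seed. Naming the imputation model in the same paragraph, including any telephone answers and 3-month data it uses, would settle how much information is really missing.

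The cost is a few lines of text and minutes of computing. The sample size, margin and data collection do not change.

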### **Data analysis**

Data was analyzed on an intention-to-treat basis. Frequency and percentages were used to describe categorical variables, Fisher's exact test used to compare treatment groups, and logistic regression used to estimate odds ratios (ORs), and associated 95% confidence intervals (95% CIs). Means and standard deviations (SDs) were used to describe approximately normally distributed continuous data. Analysis of covariance (ANCOVA) was used to compare treatment groups at 1 years after procedure adjusting for baseline values and to estimate mean differences between treatment groups and associated (95% CI). Medians and range (minimum, maximum values) were used to describe non-normally distributed continuous data, Wilcoxon rank sum test used to compare treatment groups and Student t test to estimate mean differences and associated (95% CI). Paired t tests were used for differences between pre- and post-measurements. For the primary outcome, we will also perform subgroup analysis based on body mass index (BMI) ( $< 24$ ,  $\geq 24$ ), history of POP procedure (primary, recurrent), or prolapse stage (stage 3, stage 4). Analyses will be performed for each subgroup in a similar way to the primary analysis. AEs will be listed and analyzed using a  $\chi$ -squared test or Fisher's exact test. Severe AEs will be listed and described in detail.

All data will be analyzed with SPSS 21.0 (IBM, Chicago, IL, USA) software packages. Statistical significance is defined as a two-sided P value of  $< 0.05$ .

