### **Hypothesis**

1. The composite outcome of TVM repair using self-cut mesh will be non-inferior to the TVM repair using mesh-kit.
2. TVM repair using self-cut mesh will be non-inferior to the TVM repair using mesh-kit with respect to disease-specific quality of life, sexual function scores and complications.
3. The TVM repair using self-cut mesh will be associated with lower total hospital charges than the TVM repair using mesh-kit.

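### Protocol and SAP prescribe different analyses for POP-Q and questionnaire outcomes: baseline-adjusted ANCOVA in one, comparison of changes from baseline in the other

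*Combined protocol and SAP*

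**What the plan says.** **Protocol, Data analysis (same rule in both versions).** For approximately normal continuous data: "Analysis of covariance (ANCOVA) was used to compare treatment groups at 1 years after procedure adjusting for baseline values", with a mean difference and 95% CI. For non-normal data the protocol does not adjust: "Wilcoxon rank sum test used to compare treatment groups and Student t test to estimate mean differences and associated (95% CI".

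**Original and final SAP, The secondary outcomes.** ANCOVA does not appear. The tests are given as: "We will consider the independent sample test or the non-parametric Mann-Whitney test for continuous outcomes". After a sentence on paired t tests within groups comes: "For anatomic outcomes (POP-Q score) and symptomatic improvement outcomes, we will compare the changes from baseline to 1-year follow up".

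**SAP, Analysis principles.** Baseline adjustment is conditional: "If there are any important imbalance in the baseline characteristics between groups, we will use logistic regression adjusting for baseline covariates for binary outcomes". For continuous outcomes the matching instruction is to "use linear regression analysis adjusting for baseline variables". No threshold for an important imbalance is given.

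**Protocol, Hypothesis.** The second hypothesis is non-inferiority "with respect to disease-specific quality of life, sexual function scores and complications".

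No text in either document says which of the two analyses governs.

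**The concern.** The same outcomes have two different pre-specified analyses, so the analyst could choose between them once the data are in, and the two can give different answers.

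The SAP route is also the weaker one for a mean difference. A plain comparison of change scores fixes the slope of the 1-year value on the baseline value at 1, whereas ANCOVA estimates it. When the true slope is not 1, the change score is noisier and carries part of any chance baseline difference into the treatment estimate.

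This bears on the second hypothesis. A non-inferiority claim on quality of life or sexual function needs an estimated difference with a confidence interval. The protocol's ANCOVA supplies one. The SAP promises intervals only for the primary outcome, and a Mann-Whitney test alone gives no mean difference. Precision matters most for PISQ-12, which is collected only in sexually active women.

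**Working it through.** **1. The plan's own figure.** The only computed figure is the sample size for the binary primary endpoint: (1.960 + 0.842)² × 2 × 0.9 × 0.1 / 0.1² = 141.3, rounded up to 142 per arm, or 284. Then 284/0.9 = 315.6, rounded up to 316, as in the SAP. It reproduces, but it says nothing about the continuous outcomes. I use 142 per arm below only as a scale.

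**2. The documents side by side.**

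| | Protocol | SAP |
|---|---|---|
| Approximately normal data | ANCOVA at 1 year, baseline as covariate | Change from baseline, independent-sample test |
| Non-normal data | Wilcoxon plus Student t, unadjusted | Change from baseline, Mann-Whitney |
| Baseline adjustment | Always, in the normal case | Only if an important imbalance is found |
| Difference with 95% CI | Yes | Promised for the primary outcome only |

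The SAP's list of baseline characteristics contains no POP-Q, PFDI-20, PFIQ-7 or PISQ-12 value. The listed comparison would therefore not reveal an imbalance in the covariate that matters here.

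**3. Efficiency for a mean difference.** Let r be the correlation between baseline and 1-year values, and k the baseline SD divided by the 1-year SD. In units of the 1-year variance:

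- ANCOVA: 1 - r²
- Change score: 1 + k² - 2rk
- Change score minus ANCOVA: (k - r)², which is never negative and is zero only when k = r
- Loss of effective sample: 1 - (1 - r²)/(1 + k² - 2rk), which becomes (1 - r)/2 when k = 1

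**4. Equal SDs (assumption, k = 1).** The last column gives change-score power for an effect that ANCOVA would detect with 80% power (142 per arm, two-sided 0.05).

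| r | Loss | Effective number out of 284 | CI width relative to ANCOVA | Change-score power |
|---|---|---|---|---|
| 0.1 | 45% | 156 | 1.35 | 55% |
| 0.3 | 35% | 185 | 1.24 | 62% |
| 0.5 | 25% | 213 | 1.15 | 68% |
| 0.7 | 15% | 241 | 1.08 | 73% |
| 0.8 | 10% | 256 | 1.05 | not computed |

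A simulation with 142 per arm and 4000 runs gave variance ratios (ANCOVA to change score) of 0.57, 0.65, 0.76 and 0.85 at r = 0.1, 0.3, 0.5 and 0.7. The formula gives 0.55, 0.65, 0.75 and 0.85.

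**5. Unequal SDs (assumption), r from 0 to 0.8.**

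- k = 0.5: loss of 0 to 20%. At r = 0.5, 1 - 0.75/0.75 = 0.
- k = 1.5: loss of about 56 to 69%.
- k = 2: loss of 75 to 80%. At r = 0, 1 - 1/5 = 0.80.

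**6. Chance imbalance.** If the arms differ by D at baseline, the change-score estimate is shifted by (r/k - 1)D. With k = 1 and r = 0.3 that is -0.7D, so 70% of the imbalance enters with reversed sign.

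**The case against.** **The size of the loss is not in the documents.** A reader might infer that the SAP throws away a quarter to nearly half of the effective sample. That needs equal SDs and r between 0.1 and 0.5, and the documents give no correlation or SD for any of these outcomes. Nor does it help that women enter with advanced prolapse and are expected to improve: a shift in means does not fix a correlation, and it may make the SDs unequal. This objection stands, so the figures are illustrative only.

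**Nothing was replaced.** A reader might infer that the SAP superseded the protocol's ANCOVA. The amended protocol still contains it, and the change-score sentence was already in the original SAP. This stands: it is an unreconciled conflict.

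**The contrast is narrower than it looks.** For non-normal data the protocol is unadjusted too, and the variance ratios do not carry over directly to Mann-Whitney. Operative time, blood loss, hospital stay and cost have no baseline value and are not touched. This stands.

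**The SAP sentence is loose.** It names no test, and it follows the sentence on within-group tests. The between-arm reading is an inference, as is taking the independent-sample test to be a t test. ANCOVA of the change with baseline as covariate would give the same treatment effect as ANCOVA of the 1-year value, but the tests the SAP names take no covariate. The inference is reasonable and should be labelled as one.

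**The SAP does allow adjustment.** It does, but only after an imbalance is seen, with no threshold. That is not equivalent to pre-specified adjustment.

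**Change scores are unbiased under randomisation, and no continuous secondary outcome has a sample-size target or margin.** True. The cost is precision and an open choice of analysis.

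**Conclusion.** The point holds as a conflict between documents on secondary outcomes with a baseline value. For approximately normal data the protocol adjusts for baseline and the SAP does not, unless an undefined imbalance appears. For a mean difference the SAP route cannot be more efficient in large samples.

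How much is lost cannot be determined from the documents. The equal-SD figures (10 to 45% for r from 0.8 to 0.1) and the wider range of about 0 to 80% rest on assumed values of r and the SD ratio. The primary endpoint and its power are unaffected. The change should be made because it removes a contradiction at almost no cost, not because a particular loss has been shown.

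**What to change.** In the SAP section on secondary outcomes, state that POP-Q points, PFDI-20, PFIQ-7 and PISQ-12 are compared between arms by ANCOVA of the 1-year value on arm and baseline value, reporting the adjusted mean difference and 95% CI. Include centre as well, because randomisation is stratified by it; this goes one step beyond the protocol's ANCOVA, which names only baseline values. If residuals are skewed, use a bootstrap interval or a rank-based sensitivity analysis. Treat within-arm paired tests as descriptive. Align the protocol's rule for non-normal data with this, and say which document governs. If the sponsor prefers unadjusted change scores, the SAP should record the departure from the protocol and justify it.

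The cost is a few sentences. POP-Q and the three questionnaires are already scheduled at enrolment and at 1 year, so no new data are needed.
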